##### Proximal Outcome Measures

The pilot RCT is designed to estimate the preliminary efficacy of the intervention on proximal outcome measures. These will be assessed at baseline, 4 weeks, and 8 weeks (study end point). Proximal outcome measures include (1) the Perceived Threat of AD Scale [45], a 7-item Likert-type scale assessing perceived likelihood, concern, and consequences of ADRD; (2) the Dementia Awareness Questionnaire [46], a measure of knowledge of modifiable ADRD risk factors and the Generalized Self-Efficacy Questionnaire [29], which measures self-beliefs to cope with demanding situations. The 10-item PSS and PHQ-9 will also be administered at these timepoints to minimize the risk of adverse events related to personal ADRD risk and health belief information disclosure. The procedures described will be used to ensure the safety of participants who endorse clinically significant distress or depressive symptoms.

##### Distal Outcome Measures

This pilot RCT is powered to detect changes in proximal outcome measures. We will also administer some measures pre- and posttreatment to establish the feasibility of assessment and they are (1) weight measurement; (2) blood pressure measurement; (3) venipuncture for HbA_1c_ and lipid panel (total cholesterol, LDL cholesterol, high-density lipoprotein (HDL) cholesterol, and triglycerides); (4) 14-item Mediterranean Diet Assessment Tool [47]; (5) Community Healthy Activities Model Program for Seniors (CHAMPS) Activities Questionnaire for Older Adults [47]; and (6) 25-item Florida Cognitive Activities Scale [48]. Participants will also be provided a wearable activity monitor (Fitbit [Google]) to assess physical health (eg, steps per day and heart rate variability) and sleep quality. All distal outcome measures will be considered preliminary and used to inform the design of a future, fully-powered RCT.

#### Power and Data Analysis

We estimate attrition at 10% based on our previous study investigating the basic health education intervention. Power was derived based on 3 proximal outcome measures that are likely intercorrelated (assumed 0.5 correlation). Assuming 10% attrition, a sample size of 36 could detect a medium effect (*d*=0.5) with a power of 0.80 and α=.05.

All participants, regardless of adherence or attrition, will be included in the primary intention-to-treat analysis. Primary analyses will use generalized linear mixed models to compare pre- and posttreatment change in proximal outcome measures by treatment arm. We will use *t* tests to assess group differences in feasibility benchmarks (attendance, understandability, satisfaction, and relevance) by treatment arm. Secondary analyses will examine the relationship between treatment dose (defined as class attendance) and proximal outcome measures. Given that this is a stage I pilot study, all inferential statistical results will be considered preliminary and used to assess the feasibility of the TEACH intervention. Distal outcomes will not be formally analyzed but will be used to determine the feasibility of assessment for future studies.

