### Phase 2: Pilot RCT

#### Objective

The second phase of the study is to conduct a pilot parallel-group, 2-arm RCT with 1:1 allocation to assess the feasibility and preliminary efficacy of the TEACH intervention compared to basic health education alone.

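### The primary comparison of pre-to-post change fixes neither how baseline is handled nor whether week 4 is used; read in the ordinary way, it gives up precision that costs nothing to recover

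*Protocol article*

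**What the plan says.** The Phase 2 trial is a "pilot parallel-group, 2-arm RCT with 1:1 allocation", with 40 participants randomised. Under Proximal Outcome Measures, the schedule for the perceived-threat, dementia-awareness and self-efficacy scales reads: "These will be assessed at baseline, 4 weeks, and 8 weeks (study end point".

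Under Power and Data Analysis, the primary contrast is given in one sentence: "Primary analyses will use generalized linear mixed models to compare pre- and posttreatment change in proximal outcome measures by treatment arm". The analysis set is given in another: "All participants, regardless of adherence or attrition, will be included in the primary intention-to-treat analysis". The section does not say whether the baseline means are estimated separately, constrained to be equal or adjusted for. It does not mention week 4.

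The same section claims that "a sample size of 36 could detect a medium effect (*d*=0.5) with a power of 0.80 and α=.05". It gives one correlation: "Power was derived based on 3 proximal outcome measures that are likely intercorrelated (assumed 0.5 correlation". That is the correlation between outcomes, not between a participant's baseline and week-8 score on one outcome.

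**The concern.** The usual way to fit a comparison of pre-to-post change by arm is an arm-by-time interaction in which each arm has its own baseline mean. Randomisation already makes those means equal in expectation. Estimating them separately adds noise to the treatment effect and carries part of any chance baseline gap into it.

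This matters because precision is scarce. About 18 participants per arm are expected at week 8, preliminary estimates of efficacy are among the stated primary objectives (Study Objectives and Design Overview), and the results are meant to inform a larger trial. Interval width is therefore much of what the pilot delivers.

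The silence on week 4 raises a second, smaller question: whether someone who leaves between weeks 4 and 8 contributes any post-baseline value to the primary analysis.

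**Working it through.** **Inputs.** From the article: 40 randomised 1:1, so 20 per arm; 10% attrition, so 36 in all and 18 per arm at week 8; d=0.5; α=0.05. Assumed: a two-sided test (sidedness is not stated), score SD = 1 at each visit, d on that scale, and a pre-post correlation r of 0.3 to 0.8. Power uses the normal approximation with the covariance treated as known: power = Φ(0.5/SE − 1.96).

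**1. The plan's own figure.** A between-arm difference of 0.5 SD in the week-8 score, with 18 per arm, has SE = √(2/18) = 0.333. Power is Φ(1.5 − 1.96) = 0.32 (0.31 by the t distribution), not 0.80; 0.80 needs 63 per arm. Two calculations come near the stated figure, each giving 0.83 at 36: a one-group paired t test with d=0.5, and a 2×2 group-by-time F test with f=0.25 and r=0.5. Neither is a between-arm d of 0.5. The first has no arm comparison; the second corresponds to a between-arm difference in change of 1.0 SD.

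**2. Complete cases.** Per participant, the variance of a change score is 2(1 − r), and that of a baseline-adjusted score is 1 − r². The ratio is (1 + r)/2, or 0.65, 0.75 and 0.90 at r = 0.3, 0.5 and 0.8. To this approximation it is below 1 for every r below 1.

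**3. With the expected attrition.** A likelihood-based model keeps all 20 baselines per arm. Leaving week 4 aside:

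- separate baseline means: Var = 2[(1 − r²)/18 + (1 − r)²/20]
- common baseline mean: Var = 2(1 − r²)/18

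At r=0.5 these are 2[0.75/18 + 0.25/20] = 0.1083 and 2(0.75)/18 = 0.0833.

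| Assumed r | Var, separate | Var, common | Reduction | Power, separate | Power, common |
|---|---|---|---|---|---|
| 0.3 | 0.1501 | 0.1011 | 33% | 0.252 | 0.349 |
| 0.5 | 0.1083 | 0.0833 | 23% | 0.330 | 0.410 |
| 0.8 | 0.0440 | 0.0400 | 9% | 0.664 | 0.705 |

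At r=0.5 the 95% CI half-width goes from 1.96 × √0.1083 = 0.65 SD to 1.96 × √0.0833 = 0.57 SD.

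**4. Chance imbalance.** With 20 per arm, the baseline difference has SE √(2/20) = 0.32 SD, so a gap larger than 0.3 SD in either direction has a probability of about 34%. Given a gap g, the change contrast shifts by (1 − r)g. At r=0.5 and g=0.3 that is 0.15 SD, or 30% of the 0.5 SD target. Baseline adjustment removes this shift.

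**5. What week 4 adds.** If every dropout has a week-4 value, adding that visit lowers the variance by about 0.4% to 4.5% over r = 0.3 to 0.8, under compound-symmetric or AR(1)-type correlation. If dropouts leave before week 4, it adds nothing. At r=0.5 the common-baseline variance goes from 0.0833 to between 0.0806 and 0.0824, and power to 0.41–0.42. The highest power reached anywhere in this range is about 0.73, at r=0.8.

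**The case against.** The strongest reply is that the article states neither of the features criticised. A reader might infer that it leaves baseline means free and discards week 4, but it says neither. A three-visit mixed model with a common baseline and a baseline-to-week-8 contrast also fits the sentence, and a condensed article commonly leaves model terms to the full protocol or SAP. This stands as a limit on the wording: separate baseline means are the ordinary reading, not a stated fact. It does not remove the point, because the article does name the primary contrast, names it as change, and gives one of three scheduled visits no part in it.

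A reader might also infer that dropouts contribute nothing and that the analysis rests on completers. The documents do not support that. The article commits to including all participants and to a mixed model; fitted by likelihood with baseline as a response, that model retains dropouts' baseline scores. Attrition is about 2 per arm, and the week-4 gain is small.

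Three further replies are fair. The size of the gain depends on an r that the article does not give, and the gain shrinks as r rises. A change contrast remains unbiased over randomisations, so this is a matter of efficiency, not validity. And the article calls all inferential results preliminary, which lowers the stakes, although a pilot meant to inform a larger trial still benefits from the narrower interval.

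**Conclusion.** The point holds as one of precision and clarity. On the ordinary reading of the primary contrast, the plan gives up about 33%, 23% or 9% of the variance of the arm effect at r = 0.3, 0.5 or 0.8, and leaves the estimate open to chance baseline imbalance. These figures assume equal score SDs at each visit, 20 baseline and 18 week-8 values per arm, and a known covariance; estimating the covariance in so small a sample will cost a little of the gain.

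The week-4 part is minor for precision. Its value is a post-baseline value for participants who leave after week 4, which makes the missing-at-random assumption more plausible.

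A reader might take better baseline handling as a way to reach the stated power. It is not: at r=0.5 power moves from about 0.33 to 0.41, or 0.42 at most with week 4, and it stays below 0.80 throughout the range examined. The power statement is a separate and larger problem in the same section.

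**What to change.** In Power and Data Analysis, replace the primary-analysis sentence with a specification for each proximal outcome:

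- a likelihood-based mixed model using the baseline, 4-week and 8-week scores of all randomised participants with any measurement;
- a common baseline mean across arms (constrained longitudinal data analysis), or baseline as a covariate with weeks 4 and 8 as responses;
- arm-by-time effects at weeks 4 and 8;
- the week-8 arm difference with its 95% CI as the primary estimate.

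If the full protocol or SAP already specifies such a model, bring the article's wording into line with it. The cost is wording only: all three measurements are already scheduled, and no visit, participant or procedure is added. Do not present the change as support for the stated power of 0.80.

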### Study Objectives and Design Overview

As a National Institutes of Health (NIH) stage I behavioral intervention development study, the primary objectives are to establish feasibility and preliminary estimates of the efficacy of the TEACH intervention. The objectives of this study are (1) to use qualitative methods to develop an enhanced health education intervention, including an explanatory method for communicating information about personal health beliefs, and (2) to conduct a pilot randomized controlled trial (RCT; n=20 per intervention arm) over 8 weeks to assess the feasibility and preliminary efficacy of the enhanced health education intervention versus basic health education alone on ADRD risk perception, self-efficacy, and knowledge about dementia risk. To establish the feasibility of measurement for future distal outcomes, we will collect pre- and posttreatment body weight, blood pressure measurement, hemoglobin A_1c_ (HbA_1c_) and lipid panel, and physical activity or sleep quality measured by a wearable activity monitor.

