#### Outcomes

##### Feasibility Benchmarks

A primary goal of Phase 2 is to establish the feasibility of delivering the TEACH intervention. As part of the posttreatment assessment, participants will complete 7-point Likert scales assessing the understandability, satisfaction, and perceived relevance of course material. We have established the feasibility benchmarks and they are (1) attendance—participants attend at least 75% of classes (12 of 16), (2) understandability—80% of participants agree or strongly agree that the material was understandable, (3) satisfaction—80% of participants agree or strongly agree that the program was satisfying, and (4) relevance—80% of participants agree or strongly agree that the material was relevant to their personal situation.

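### The feasibility benchmarks for TEACH name no arm, and the only analysis stated for them, a between-arm t test, cannot show whether TEACH meets a fixed threshold

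*Protocol article*

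**What the plan says.** Under Feasibility Benchmarks, the protocol article states: "A primary goal of Phase 2 is to establish the feasibility of delivering the TEACH intervention". Study Objectives and Design Overview puts efficacy beside it: "the primary objectives are to establish feasibility and preliminary estimates of the efficacy of the TEACH intervention". Feasibility is therefore one of two primary aims.

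Four benchmarks follow, each an absolute level:

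- Attendance: "participants attend at least 75% of classes (12 of 16".
- Understandability: "80% of participants agree or strongly agree that the material was understandable".
- Satisfaction: "80% of participants agree or strongly agree that the program was satisfying".
- Relevance: "80% of participants agree or strongly agree that the material was relevant to their personal situation".

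The last three come from 7-point Likert ratings collected in both arms at the posttreatment assessment. No benchmark says whose participants are counted. The attendance benchmark also does not say what share of participants must reach 12 classes.

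Under Power and Data Analysis, the only analysis given for these four items is t "tests to assess group differences in feasibility benchmarks (attendance, understandability, satisfaction, and relevance) by treatment arm". The primary analyses are mixed models of the proximal outcomes by arm. The section then says that "all inferential statistical results will be considered preliminary and used to assess the feasibility of the TEACH intervention".

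**The concern.** The benchmarks ask whether TEACH reaches a set level. The t test asks whether TEACH differs from basic health education. These are different questions, and the answer to the second does not settle the first. The quantity may differ too. A t test on 7-point ratings compares mean scores, whereas the benchmark is the share who agree or strongly agree.

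With no arm named, the 80% could be taken over all 40 participants. A well-liked control arm could then lift the total past the line.

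The sentence on inferential results widens the problem. Those results include the models of perceived threat, dementia awareness and self-efficacy, and none of these measures whether the programme can be delivered.

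The Discussion says the results will inform the design of a fully powered trial, so an unclear feasibility verdict would carry forward.

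**Working it through.** **Inputs from the article.** 20 per arm, 40 in total; 10% attrition, so 40 × 0.9 = 36, about 18 per arm; benchmark 80%; attendance 12/16 = 75%. The article gives no sample-size reasoning or operating characteristics for the benchmarks, so there is no figure of its own to reproduce here beyond this arithmetic.

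**Assumptions.** The article gives no expected agreement rates. I use three pairs (TEACH/basic): 75%/85%, 70%/90% and 65%/95%. Each averages 80%. Ratings are scored agree = 1, otherwise 0, so that the t test and the benchmark concern the same quantity. This favours the t test.

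**Step 1. Does the t test track the threshold?** With *n* per arm and observed shares a and b, t = (a − b) / √{[a(1 − a) + b(1 − b)] / (n − 1)} on 2n − 2 degrees of freedom. At n = 20:

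| TEACH | Basic | t | p | TEACH against 80% |
|---|---|---|---|---|
| 12/20 = 60% | 12/20 | 0 | 1.0 | misses |
| 18/20 = 90% | 18/20 | 0 | 1.0 | meets |
| 16/20 = 80% | 20/20 | −0.20/0.0918 = −2.18 | 0.036 | meets |
| 14/20 = 70% | 18/20 | −0.20/0.1257 = −1.59 | 0.12 | misses |

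The first two rows give the same test result with opposite benchmark results. The last two give a significant deficit where TEACH meets the benchmark and a non-significant one where it misses.

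**Step 2. What the choice of arm does.** In the last row the total is 14 + 18 = 32, and 32/40 = 80%. This is a pass over both arms, with TEACH at 70%.

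**Step 3. How often that could happen.** Let T and B be the numbers agreeing, binomial with the assumed rates. The chance that the pooled rule passes while TEACH is observed below 80% is the sum, over values t of T below the TEACH threshold, of P(T = t) × P(B ≥ pooled threshold − t).

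- At 20 per arm the thresholds are 16/20 and 32/40.
- At 18 per arm they are 15/18 and 29/36, since 0.8 × 18 = 14.4 and 0.8 × 36 = 28.8, both rounded up.

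| Assumed true rates, TEACH/basic | 20 per arm | 18 per arm |
|---|---|---|
| 75%/85% | 0.22 | 0.29 |
| 70%/90% | 0.36 | 0.40 |
| 65%/95% | 0.48 | 0.49 |

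**Step 4. What a TEACH-only reading gives.** The exact (Clopper-Pearson) 95% interval is 56.3% to 94.3% for 16/20, and 58.6% to 96.4% for 15/18.

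**The case against.** Several points on the other side are sound.

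- **The comparison has a purpose.** The Phase 2 objective sets TEACH against basic health education, and the Discussion hypothesizes higher adherence with TEACH. Attendance counts and 7-point ratings are commonly compared by means. The t tests are therefore legitimate for that comparison and need not be removed.
- **The benchmarks can be read without a test.** An observed percentage can simply be set against 80%, and a condensed article need not spell out such a tabulation. That would dispose of the point if the article were merely silent. It is not silent: it names one analysis for these four items, which does not address the thresholds, and it leaves the arm open. An analysis plan that followed it would inherit both.
- **Pooling is not stated.** The benchmark paragraph opens with delivery of TEACH and the analysis is by arm, so a TEACH-only reading is the more natural one. The probabilities in Step 3 describe a possible reading, under assumed rates.
- **The sentence on inferential results is mainly a caution** that a pilot's results are preliminary. That stands, but its last clause still names feasibility as their use.

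A reader might infer more: that the t tests replace the benchmarks, that feasibility is the sole primary goal, or that a non-significant efficacy result would count against feasibility. The article supports none of these. It calls feasibility a primary goal beside preliminary efficacy, never says that the thresholds are set aside, and gives no rule linking an efficacy p value to the verdict. Nor does it show harm that a t test is non-significant about 95% of the time when both arms share the same rate. That only restates α = .05.

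**Conclusion.** The point holds as a mismatch within the article. Absolute benchmarks for TEACH are paired with a between-arm test that cannot show whether they are met, the benchmarks name no arm, and efficacy inference is said to inform feasibility.

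That the test cannot show whether a threshold is met needs no assumed rates; the p values in Step 1 are for ratings scored agree or not. The size of the arm problem does depend on assumptions: if the 80% were read over both arms, the chance of a pooled pass with TEACH observed below 80% is 0.22 to 0.48 at 20 per arm and 0.29 to 0.49 at 18 per arm, for the three assumed pairs. Under the more natural TEACH-only reading that risk disappears, which is why the article should state it.

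This should be corrected before the feasibility data are analysed. It does not invalidate the design.

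**What to change.** 1. In Feasibility Benchmarks, state that the benchmarks are judged in the TEACH arm.
2. For understandability, satisfaction and relevance, compare the observed TEACH share with 80% and report an exact 95% confidence interval.
3. For attendance, report the TEACH share attending at least 12 of 16 classes with an exact 95% confidence interval, and state the share required. Without that share the benchmark cannot be judged as met or missed.
4. In Power and Data Analysis, keep the between-arm comparison of attendance and ratings, labelled secondary and descriptive, and say that it does not decide feasibility.
5. Reword the end of the sentence on inferential results so that efficacy inference is preliminary and does not feed the feasibility verdict.

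The cost is wording only, with no change to data collection or sample size. The downside is that the TEACH-only estimate rests on about 18 to 20 people, and its wide interval will be on view: even an observed 80% is compatible with a true share from 56% to 94%.

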## Results

This project was funded in August 2022. Data collection is ongoing, with 26 individuals enrolled to participate in focus groups and 11 enrolled to complete individual interviews (phase 1) by the submission of this study in May 2024. Enrollment into the RCT (phase 2) is anticipated to begin in 2024, with completion of enrollment and data analysis anticipated in 2025.

## Discussion

The goal of this study is to develop a personalized, multidomain behavioral intervention to promote long-term maintenance of health behaviors for primary prevention of ADRD in midlife and establish the feasibility of delivering this type of intervention. Despite a robust body of evidence describing modifiable health behaviors that could reduce the global dementia burden by 40% [2], multidomain behavioral interventions for the primary prevention of dementia have been hampered by poor adherence [14,15]. This study uses behavioral science to educate individuals about the intrapersonal factors that promote and maintain health behavior change (ie, understanding why we behave the way we do in addition to educating people about what behaviors are optimal). We hypothesize that this personalized approach will result in higher treatment adherence and greater efficacy of a multidomain health education intervention.

Very little research to date has used personalized intervention to promote health behavior change specifically for primary prevention of dementia. One of the challenges in dementia prevention is that individuals must maintain health-promoting behaviors like dietary changes and exercise for years to avert or delay an adverse outcome (dementia) that is perhaps decades away. Thus, effective interventions must focus on the maintenance of health behavior change over the long term. One recently completed trial, the SMARRT intervention, used motivational interviewing to assess participants’ values and motivators to reduce Alzheimer risk and help them adopt specific, achievable risk-reduction steps [10,49]. Participants in the active intervention showed greater improvements in cognition, dementia risk factors, and quality of life. However, the SMARRT trial enrolled participants aged 70 to 89 years, whereas our intervention is designed to target midlife adults aged 40-69 years. Additionally, the TEACH intervention adopts the HBM and will specifically educate people about intrapersonal processes that may promote health behavior.

This stage I intervention development project aims to use a mixed methods approach to refine a multidomain behavioral health intervention for primary prevention of dementia in midlife and early late life (age 45-69 years). The first phase of the project will use qualitative methods, including focus groups and individual interviews, to develop the personalized health education intervention (TEACH). This will include the development of an explanatory method for communicating information about personal health beliefs that is perceived to be acceptable, appropriate, and applicable to participants. The second phase of the project includes a pilot RCT to examine the feasibility and preliminary efficacy of the TEACH intervention compared to basic health education on personal dementia risk perception, dementia knowledge, and self-efficacy. If successful, this study will contribute new knowledge about personalized health education for primary prevention of dementia and a framework for educating individuals about intrapersonal processes that may be barriers or facilitators of health behavior change. Results will be used to inform intervention development and design a fully powered RCT to determine the efficacy of the TEACH intervention versus basic health education alone.

